# Section III: Subjects

1. **Briefly describe the number and characteristics of participants required for the study, and how a potential sample of such participants will be identified.**

Participants will include approximately 58 women residing in Saskatchewan seeking TAICBT treatment for symptoms of PPD. Potential participants will respond to advertising for *Maternal Depression Online* or will be referred by healthcare providers. Next, participants will be screened through questions on the Online Therapy USER website and by telephone to determine if they are eligible for TAICBT services and whether this form of service is appropriate for their concerns.

A woman will be deemed eligible to participate if she is a Saskatchewan resident, 18 years or older, meets diagnostic criteria for major depression or sub-clinical depression, and has a child under 12 months of age. Diagnostic criteria for PPD and sub-clinical PPD will be determined using cut-off scores on the Edinburgh Postnatal Depression Scale (Cox et al., 1987; see Appendix C) and a structured clinical interview for psychological disorders (MINI; Sheehan et al., 1998; See Appendix E).Participants will also be required to have regular access to a computer and the internet and endorse familiarity and comfort with using them. Lastly, participants will need to provide a contact name and number of a physician or another medical contact as this contact will be notified of the client’s participation in the online treatment program (see Appendix N).

Participants will be excluded from the study if they do not meet the above criteria or if they are (a) currently receiving psychotherapeutic treatment elsewhere or in some other form; (b) meet criteria for current substance abuse or dependence (drugs or alcohol); (c) meet criteria for a current psychotic disorder or bipolar disorder, or severe symptoms of depression, including suicidal ideation; or (d) report having a serious medical condition that may interfere with treatment completion.

2. Describe the recruitment procedures. Who will approach potential participants (researcher, assistant or third party) and how (e.g. by phone, mail)?

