   **Client understands confidentiality.**

| ***Demographic Data*** | | | | |
| --- | --- | --- | --- | --- |
| Client Name: | Date of Birth (DD/MM/YYYY) | | | |
| Address: | Appt #: | | | |
| City: | Postal Code: | | | |
| Phone No.:(home)  (work)  (other)  Phone No. during the day: | Can we contact you by: (Y or N)  Phone _______ Letter______  Leave Message____ **Email**____ | | | |
| Health Card No.: |  | | | |
| ***Exclusion Criteria*** | | | |  |
|  | | **Appropriate** | **Not Appropriate** |  |
| 1. Are you a Saskatchewan resident? | | Yes | No |  |
| 2. How old are you? _________ years | | Over 18 | Under 18 |  |
| 3. Do you have a **child** under the age of **one**? | | Yes | No |  |
| 4. Do you have access to a computer and printer at home? | | Yes | No |  |
| 5. Do you have access to the Internet at home? | | Yes | No |  |
| 6. Do you feel comfortable using the Internet? | | Yes | No |  |
| 7. Do you feel comfortable writing e-mails? | | Yes | No |  |
| 8. Would you be willing to have your physician, a medical clinic, or an emergency hospital be notified of your participation in this program?  Doctor’s Name:_________________________________  Medical Clinic:__________________________________  Telephone Number:_______________________________ | | Yes | No |  |

9. How far did you go in school?

Less than Grade 6  College/technical certificate; some university

Less than Grade 9  University undergraduate degree(s)

Less than Grade 12  University graduate degree(s)

High school diploma or GED

10. How comfortable would you say you are with writing out your thoughts and describing your feelings in words? Would you say you are…

| *Not very comfortable* | *A little comfortable* | *Somewhat comfortable* | *Fairly comfortable* | *Very comfortable* |
| --- | --- | --- | --- | --- |
| 1 | 2 | 3 | 4 | 5 |

11. Do you have any concerns about your ability to read or write?

______________________________________________________________________________

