**In the past month did you:**

B1 Suffer any accident? This includes taking too much of your medication accidentally. NO YES 0

IF NO TO B1, SKIP TO B2; IF YES, ASK B1a:

**B**1a Plan or intend to hurt yourself in any accident either actively or passively (e.g. by not avoiding a risk)? NO YES 0

IF NO TO B1a, SKIP TO B2: IF YES, ASK B1b:

B1b Intend to die as a result of any accident? NO YES 0

B2 Feel hopeless? NO YES 1

B3 Think that you would be better off dead or wish you were dead? NO YES 1

B4 Think about hurting or injuring yourself or have mental images of harming yourself, NO YES 4 with at least some intent or awareness that you might die as a result?

How many times? _____

B5 Think about suicide (killing yourself)? NO YES 6

How many times? _____

IF NO TO B5, SKIP TO B7. OTHERWISE ASK:

Frequency Intensity

Occasionally πMild π

Often πModerate π

Very often πSevere π

B6 Feel unable to control these impulses? NO YES 8

| B7 | Have a suicide method or plan in mind (e.g. how, when or where)? | NO | YES | 8 |
| --- | --- | --- | --- | --- |

IF NO TO B7, SKIP TO B9.

NOTE: IF PARTICIPANT HAS A SUICIDE PLAN OR RESPONDS ‘YES’ TO ANY OF THE ITEMS FROM B7 ONWARD, END INTERVIEW AND REFER TO ALTERNATIVE RESOURCES.

B8 Intend to follow through on a suicide plan? NO YES 8

B9 Intend to die as a result of a suicidal act? NO YES 8

B10 Take any active steps to prepare to injure yourself or to prepare for a suicide attempt

in which you expected or intended to die? NO YES 9

How many times? _____

B11 Injure yourself on purpose without intending to kill yourself? NO YES 4

B12 Attempt suicide (to kill yourself)? NO YES 9

A suicide attempt means you did something where you could possibly be injured,

with at least a slight intent to die.

IF NO, SKIP TO B13:

How many times? _____

Hope to be rescued / survive π

Expected / intended to dieπ

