**In your lifetime:**

B13 Did you ever make a suicide attempt (try to kill yourself)? NO YES 4

“A suicide attempt is any self-injurious behavior, with at least some intent (> 0) to die as a result or if intent can be inferred, e.g. if it is clearly not an accident or the individual thinks the act could be lethal, even though denying intent.”

(C-CASA definition). Posner K et al. Am J Psychiatry 164:7, July 2007.

| is at least **1** of the above (EXCEPT B1) coded **yes**?  If yes, add the total points for the answers (B1-B13)  checked ‘yes’ and specify the suicidality score as indicated in the diagnostic box:  make any additional comments about your assessment of this patient’s current  and near future suicidality in the space below:  If you do start having thoughts of suicide, or you begin to have a plan around suicide during this program, please make sure to let your therapist know. Since your therapist may not check their emails every day, it would be best if you phone them. You can also phone the Online Therapy Unit and speak to the co-ordinator for this project, [name]. If you are unable to reach your therapist or the co-ordinator, there is a suicide prevention tab on the website that lists other agencies you can call as well. If you feel as though you are at risk for committing suicide, you can also call 911 for help. | ***NO YES***  ***SUICIDALITY***  ***CURRENT***  1-8 points Low π  9-16 points Moderate π  > 17 points High π   |
| --- | --- |

**Participant must have LOW Current Suicide Risk to participate in program. If > Low, DISCUSS OTHER OPTIONS FOR TREATMENT; DOCUMENT DISCUSSION; CONSULT WITH SUPERVISOR IMMEDIATELY.

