| K14 is **K13** coded **yes**  **or**  are 1 or more « a » questions from K1a to K6a, coded **yes bizarre**?  **or**  are 2 or more « a » questions from K1a to K7a, coded **yes** (rather than **yes bizarre**)    and did at least two of the psychotic symptoms occur during the same 1 month period? | **NO YES**  ***PSYCHOTIC DISORDER***  **LIFETIME**  **NOTE: If ‘YES’, END INTERVIEW and REFER to ALT. RESOURCES** |
| --- | --- |

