**APPDENDIX W. PROTOCOL TO ADDRESS A CLIENT WHO IS AT RISK OF SUICIDE**

During the screening process, potential clients are asked a series of suicidality questions. If an individual being screened endorses items that suggest suicidal ideation, the screener must adhere to the following steps:

1) Establish rapport with the client and communicate to her willingness to help. Listen to the client in a concerned and empathetic manner, while also assessing their suicidal potential. The questions to obtain the individual’s suicidal potential are located within the Full Screen Interview under the *Suicidality* section in the M.I.N.I. (see Appendix E, Module B). The screener MUST ask all of these questions to adequately assess the individual’s suicide risk. These questions include information on the frequency, intensity, and duration of these thoughts, the specifics of a potential suicide plan, and the individual’s history around suicidality.

2) If the individual receiving screening does have a suicide plan, the screener will ensure that they have all the information about this plan using the SLAP acronym, which includes information regarding the following factors:

- Specificity of the plan: The more specific the plan, the greater the risk of suicide.
- Lethality of the method: The greater the lethality, the higher the risk of suicide.
- Inquire about the general method and how method will be employed.
- Availability of the method.
- Proximity of social or helping resources: The further the client is from support the greater the risk.

Once the screener has assessed the potential client’s suicide risk, they will decide on an appropriate course of action based on the client’s risk of suicide. They should seek supervision as soon as possible for this situation. They must also document the screening, as well as the actions they took.

If the client is at ***high risk*** for suicide (e.g., specific plan, lethal and available method, resources are limited), then the screener should encourage this person to seek immediate medical attention from their physician. If their physician is unavailable, then they should be directed to the emergency room of the nearest hospital. This potential client should be asked to contact someone they feel comfortable speaking with to assist them in going to the doctor or to the hospital.

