If the plan appears immediate, the screener is to call 911. The screener should also let the potential client know that they will need to contact their physician to ensure that he or she is aware of their client’s situation, and so that they can monitor the client’s status.

In regards to ***medium suicide risk***, the screener will encourage the client to seek assistance from their local mental health clinic. The screener must also provide the potential client with the mental health clinic’s contact information (i.e., phone number, address). They may also consider contacting the family physician to make him or her aware of the client’s difficulties. If the screener is going to contact the physician, they must let this potential client know.

In the case of ***low risk*** suicidality, the screener should seek a supervisor out in order to determine if the risk of suicide is sufficiently low for the client to participate in online therapy, or if the client should be encouraged to seek in person services. Actions will be taken based on this decision.

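### Section III, Appendix E and Appendix W give different eligibility rules for the same suicidality answers, and two interview instructions that cannot both be followed

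*Protocol*

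**What the plan says.** **Section III, item 1 (exclusions).** Exclusion (c) covers women who "meet criteria for a current psychotic disorder or bipolar disorder, or severe symptoms of depression, including suicidal ideation". No score or severity threshold is attached. Item 3 of the same section makes the telephone interviews the means of applying the criteria.

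**Appendix E, Module B (MINI suicidality).** Points are printed beside each item, for example "B5 Think about suicide (killing yourself)? NO YES 6". The bands are 1 to 8 Low, 9 to 16 Moderate and above that High. Below the score box stands "Participant must have LOW Current Suicide Risk to participate in program", with immediate supervisor consultation if the result is above Low. A note after B7 covers a plan or a yes to any "ITEMS FROM B7 ONWARD, END INTERVIEW AND REFER TO ALTERNATIVE RESOURCES".

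**Appendix W.** It applies when a woman being screened endorses items suggesting suicidal ideation. It says of Module B: "The screener MUST ask all of these questions to adequately assess the" person's suicide risk, and where there is a plan the screener must obtain all the information about it. At low risk, "the screener should seek a supervisor out in order to determine if the risk of suicide is sufficiently low for the client" to take part online.

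**Psychosis and equipment.** Section III excludes current psychotic disorder. In Appendix E, Module G, the lifetime boxes as well as the current ones carry the instruction "END INTERVIEW and REFER to ALT. RESOURCES". Section III asks for regular access to a computer and the internet. Appendix B asks "4. Do you have access to a computer and printer at home" and has a similar item on home internet; a no to either is marked not appropriate.

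**The concern.** The form is the tool that applies the Section III criteria, so the two must give the same answer for the same woman. For a woman who reports suicidal thoughts they do not: one place excludes her, one does not bar her, and one leaves her to a case-by-case decision. If she is randomised, she is a protocol violation on one reading and properly enrolled on another. With about 58 women planned, each such case is 1/58 = 1.7% of the sample. Women randomised to the waitlist wait 7 to 10 weeks and are then re-screened against the same criteria, so the ambiguity arises a second time for them.

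The interview instructions raise a separate problem. When a woman discloses a plan, the form tells the screener to stop and Appendix W tells the screener to continue.

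**Working it through.** **1. Inputs.** Points printed in Appendix E, Module B: B2 = 1, B3 = 1, B4 = 4, B5 = 6, B6 = 8, B7 = 8, B8 = 8, B9 = 8, B10 = 9, B11 = 4, B12 = 9, B13 = 4. Printed skips: no at B5 goes to B7; no at B7 goes to B9. The score is the sum of points for items answered yes. I count B4 and B5 as suicidal ideation.

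**2. Low scores with ideation and no yes from B7 onward.**

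| Items answered yes | Sum | Band |
|---|---|---|
| B4 | 4 | Low |
| B2 + B4 | 1 + 4 = 5 | Low |
| B3 + B4 | 1 + 4 = 5 | Low |
| B2 + B3 + B4 | 1 + 1 + 4 = 6 | Low |
| B5 | 6 | Low |
| B2 + B5 | 1 + 6 = 7 | Low |
| B3 + B5 | 1 + 6 = 7 | Low |
| B2 + B3 + B5 | 1 + 1 + 6 = 8 | Low |

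The list is complete: B4 + B5 = 10, and B6 needs B5, giving at least 6 + 8 = 14. Both are Moderate. If only B5 counts as ideation, four patterns remain. If B3 also counts, B3 alone and B2 + B3 are added, making ten.

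**3. The rules applied to these eight patterns.**
- Section III, plain reading: excluded.
- Appendix E: the Low requirement is met and the stop note is not triggered, so nothing bars her.
- Appendix W: at low risk a supervisor decides.
- Supervisor contact: Appendix E requires it only above Low; Appendix W requires it at Low.

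**4. The rest of the Low band.** In all, 24 patterns total 1 to 8. Three contain only B2 and/or B3, eight are those above, and 13 contain a yes from B7 onward (3 + 8 + 13 = 24). Among the 13 are B7 alone (8), B11 alone (4) and B13 alone (4). For them the score says Low and the stop note says refer, so the woman is referred out. B7 with any other scored item is at least 8 + 1 = 9, Moderate. One of the 13, B11 + B13 = 8, cannot arise if the stop note is followed, because a yes at B11 ends the interview before B13.

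**5. Stop versus ask all.** Suppose the first yes is at B7. Stopping leaves B8 to B13 unasked. They carry 8 + 8 + 9 + 4 + 9 + 4 = 42 points, so the full total could lie anywhere from 8 (Low) to 8 + 42 = 50 (High). The score cannot be completed, and the Appendix W instruction to ask every question cannot be met.

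**6. Psychosis and equipment.** The forms turn away women with a lifetime but not current psychotic disorder, and women with regular access but without a computer, printer or internet at home. Section III would not exclude either group on these grounds. The mismatch runs one way: the forms are stricter.

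**The case against.** **The rules can be read as successive filters.** Appendix E makes a Low score a necessary condition, not a sufficient one. A reader might infer that the form admits everyone scoring 1 to 8; the text does not say so, and Appendix W adds the supervisor step. This stands, but it does not remove the conflict. Where Section III excludes outright there is nothing left for a supervisor to decide, yet Appendix W, which is written for women who have endorsed ideation items, leaves entry open at low risk.

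**Section III may mean ideation only within severe depression.** It is a brief description, and ideation appears as an instance of severe symptoms. The Appendix E script also speaks of suicidal thoughts starting during the program, which suggests that women are expected to enter without them. Either reading is possible, but they point in opposite directions and no threshold settles the matter.

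**A reader might infer that a woman with a plan can be admitted.** The documents do not support this. B7 scores Low only as the sole scored yes, and the stop note names that case and refers her out. The same holds for B11 and B13.

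**A reader might infer that the stop note cuts off the safety response.** That is not shown. The note can be read as ending the eligibility interview, with Appendix W taking over. Even so, Module B carries no cross-reference to Appendix W, and asking every question does not fit with stopping at B7.

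**A reader might infer that screeners would in practice admit different women.** That too is not shown: all use the same form, and low-risk cases go to a supervisor.

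**Conclusion.** The concern holds for two conflicts. First, for eight Low-scoring answer patterns (four to ten, depending on which items count as ideation), the documents give different eligibility rules and disagree on when a supervisor is consulted. Second, the stop from B7 onward and the instruction to ask every question cannot both be followed, and a stopped interview leaves the score incomplete. The second conflict does not depend on how Section III is read; the first rests on its plain reading.

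For B7, B11 or B13 alone, score and stop note merely disagree, and the woman is referred out. The psychosis and equipment mismatches are minor: the screened population would be slightly narrower than the stated one. They would not justify an amendment by themselves.

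The documents do not say how many screened women would give the affected answers, so the number of enrolments at issue cannot be estimated. Eligibility is settled before random assignment, so on the stated sequence the ambiguity blurs who was studied and does not in itself favour either arm. It still needs correcting, because it governs who is randomised and what a screener does when a plan is disclosed.

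**What to change.** Reconcile Section III item 1, the Module B stop note and Low-risk requirement in Appendix E, and Appendix W into one suicidality eligibility rule and one interview sequence. Use the same wording in all three places. The text should settle:
- how ideation items bear on eligibility;
- how the Appendix W risk levels relate to the Module B score;
- at which levels a supervisor is consulted;
- how the stop note and the Appendix W questions fit together.

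The clinical team decides the content of each; this review takes no position on which rule is right.

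In the same edit, align Section III with Appendix E, Module G (current or lifetime psychosis) and with Appendix B (regular access, or computer, printer and internet at home).

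The cost is a wording amendment to Section III and Appendices B, E and W as needed, best made before screening starts. It requires no new measure and no change to the sample size or analysis.

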All potential participants will participate in a telephone pre-screening and full-screening interview. When participants first contact the researcher, they will be informed of the nature of the study including the potential to be randomized to a waitlist condition (see Appendix X). The pre-screen interview will take approximately 15 minutes and will inquire about referral source, demographic questions, and questions about their symptoms (see Appendix B). To assess for severity of depressive symptoms, the Edinburgh Postnatal Depression Scale (Cox et al., 1987) will also be administered (see Appendix C). The full-screen interview will include additional demographic questions as well as the administration of the M.I.N.I. International Psychiatric Interview (M.I.N.I; Sheehan et al., 2006; see Appendices D and E). These interviews will be used to determine if they meet the inclusion and exclusion criteria established for the study.

As the current project is a randomized controlled trial, following the telephone screening and assessments, if the participant is eligible and interested in participating, she will be randomly assigned to either receive TAICBT treatment or to a 7-10 week waitlist group. Participants in both groups will be provided with a website link to a secure Canadian survey program (fluidsurveys.com). An information form and a consent form will be presented for the specific groups (see Appendices F and G). Each group will then be presented with a battery of baseline outcome measures (see Appendices H to M). These measures will take approximately 30 minutes to complete and will assess symptoms related to PPD, general stress, parental stress, quality of life, and treatment expectations.

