When participants first contact the unit they will be provided with a brief description of the study including the potential of being randomized to a 7-10 week wait list condition (see Appendix X). At this time a brief description of the Maternal Depression Online program will also be provided (i.e., number of modules, description of topics covered, the online therapist’s involvement in the client’s treatment). If a participant indicates interest in participation, she will be administered the prescreening interview (see Appendix B). If deemed eligible after the pre-screen interview, participants will be asked to participate in a more comprehensive telephone assessment (see Appendix D). They will be asked to verbally consent prior to starting this assessment (see Appendix D). If a participant is determined to be eligible to participate in the study after the telephone assessments, they will be notified if they have been randomized to receive TAICBT right away or if they will receive a pamphlet and informed that they will be offered the TAICBT after a 7-10 week wait period. At this time, they will be sent a website link that will include a consent form describing their role in participating, depending on which group they are assigned to (see Appendices F and G).

5. Will a consent form be used? If so, when will it be presented (e.g. immediately before interviews take place)?

Information and consent forms will be presented to the TAICBT participants (see Appendix G) and to the pamphlet control group participants (see Appendix F). Both consent forms will be presented online prior to completing baseline outcome measures. Prior to this, verbal consent will be obtained when participants undergo the comprehensive telephone assessment (see Appendix D). Participants assigned to the pamphlet control condition will also receive a consent form prior to starting the TAICBT treatment (see Appendix V).

6. a)Will participants be anonymous in the data gathering phase of the study?(Anonymous means that no link can be established between the participant and the research – no one including the researcher knows who has participated in the research)

No  Yes, the researcher only  Yes, no one including the researcher knows

1. Will the confidentiality of participants and their data be protected? (Confidentiality means that no link can be established between the collected information and the participant’s identity)

No

Yes

Yes, with the following limits:

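### Women are randomised and told their arm before the online consent form and before the baseline DASS-21, PSI-SF and WHOQOL-BREF, so these three baselines and consent itself can depend on allocation

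*Protocol*

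**What the plan says.** Section III, item 3 sets out the steps. The telephone pre-screen includes the EPDS: "To assess for severity of depressive symptoms, the Edinburgh Postnatal Depression Scale (Cox et al., 1987) will also be administered". The full screen adds the MINI and further demographic questions. An eligible and interested woman is then allocated: "she will be randomly assigned to either receive TAICBT treatment or to a 7-10 week waitlist group". A survey link follows, and with it the consent form: "An information form and a consent form will be presented for the specific groups (see Appendices F and G". The battery comes last: "Each group will then be presented with a battery of baseline outcome measures (see Appendices H to M". Among those appendices, the DASS-21, PSI-SF and WHOQOL-BREF are the efficacy outcomes completed by both arms.

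Item 4 confirms that the arm is disclosed before any of the online steps. Once found eligible, "they will be notified if they have been randomized to receive TAICBT right away or if they will receive a pamphlet". It continues: "At this time, they will be sent a website link that will include a consent form describing their role in participating", with a form that differs by group. Item 5 fixes the rest of the order: "Both consent forms will be presented online prior to completing baseline outcome measures". The only consent before allocation is verbal: "Prior to this, verbal consent will be obtained when participants undergo the comprehensive telephone assessment".

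The Analysis paragraph of the study summary bases efficacy on repeated-measures mixed-model ANOVAs and classifies clinical significance by the Jacobson-Truax method. Both use the pre-treatment score.

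**The concern.** A baseline score is useful because allocation cannot have influenced it. Here three of the outcome scales are answered by women who came looking for online therapy and have just learned either that it starts now or that they will get a pamphlet and wait 7 to 10 weeks. Mood, stress and quality of life are the constructs in which a reaction to that news would show. Any such reaction sits in the pre score, and a pre-post comparison treats it as part of the change. The planned tests of baseline differences between groups cannot separate chance imbalance from reaction to allocation.

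The second problem is who remains. A woman may decline the arm-specific form, or abandon a survey of about 30 minutes, after learning her arm. These losses occur after randomisation and may differ between arms. With 58 women planned, a few unequal losses would weaken the comparison on every post-treatment outcome, including the EPDS.

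**Working it through.** **Order of events.** Items 3, 4 and 5 of Section III, read together, give:

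1. First contact: the study is described, including possible waitlisting.
2. Telephone pre-screen, with EPDS.
3. Verbal consent, then the full telephone assessment, with MINI and demographics.
4. Random assignment.
5. Arm disclosed and link sent.
6. Arm-specific online consent form.
7. Baseline DASS-21, PSI-SF and WHOQOL-BREF.
8. TAICBT login issued (TAICBT arm).

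The battery is therefore before treatment but after allocation and disclosure. Nothing in the protocol puts step 6 or 7 ahead of step 4.

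**Effect of a baseline shift.** The protocol gives no effect size, SD, alpha or power, so it has no calculation to reproduce. What follows is illustration. Only the total of 58 comes from the protocol. The assumptions are 29 per arm (the allocation ratio is not stated), two-sided alpha 0.05, equal SDs, and pre-post correlation ρ = 0.5 with a range of 0.3 to 0.7.

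Score every scale so that higher is better. The group-by-time estimate is (post − pre) in TAICBT minus (post − pre) in waitlist. If knowing the arm makes the TAICBT mean better than the waitlist mean by b SD at baseline, and this has gone by post-treatment, the estimate falls by b. If the shift runs the other way, the estimate rises by b.

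Standard error of the difference in change, in SD units: √(2(1 − ρ)) × √(2/29). At ρ = 0.5 this is 1 × 0.2626 = 0.263.

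*Shift that makes TAICBT look better at baseline, b = 0.2, true effect 0.75 SD.* The expected estimate is 0.75 − 0.20 = 0.55 SD. The noncentrality falls from 0.75/0.2626 = 2.86 to 0.55/0.2626 = 2.09. With 56 degrees of freedom (noncentral t), power falls from 80% to 54%.

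*Shift in the other direction, no true effect.* The noncentrality is b divided by the SE, and the two-sided rejection rates are:

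| b (SD) | ρ = 0.3 | ρ = 0.5 | ρ = 0.7 |
|---|---|---|---|
| 0 | 5% | 5% | 5% |
| 0.1 | 6.2% | 6.6% | 7.7% |
| 0.2 | 9.7% | 11.6% | 16.2% |
| 0.3 | 15.8% | 20.2% | 30.5% |

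A baseline-adjusted analysis would reduce the bias from b to ρb, for example 0.5 × 0.2 = 0.10 SD, but would not remove it.

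**The case against.** Several points on the other side are sound and limit the finding.

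- **The EPDS is clean.** It is given at the pre-screen, before allocation, and sits outside the Appendix H to M battery. A reader might infer that every efficacy test has a compromised baseline. The protocol does not support that: if the screening score is used, the depression measure designed for this population has a baseline that allocation could not have touched.
- **Refusers are not unknown.** A reader might infer that women who leave after allocation leave no baseline data. In fact the EPDS, MINI, demographics, medication and treatment history are collected by telephone beforehand, so refusers can be described by arm. Only the three online scales would be missing.
- **Women are not randomised unawares.** They hear of possible waitlisting at first contact, confirm their interest, and give verbal consent before the full assessment. That consent is tied to the telephone assessment, however, and the trial consent form still follows disclosure.
- **The natural reactions work against the treatment.** Relief in the TAICBT arm and disappointment in the waitlist arm both make TAICBT look better at baseline and so shrink its apparent gain. A reader might infer that the main danger is a false-positive result; that does not follow from this mechanism.
- **The shift may be small or may cancel.** The DASS-21 asks about the past week and the WHOQOL-BREF about the last four weeks, periods that may lie largely before allocation. A reaction that persisted unchanged to post-treatment would cancel in the change score.

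None of this changes the stated order or makes the three online baselines independent of allocation. Nor does it prevent refusal from depending on the arm.

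**Conclusion.** The concern stands for the DASS-21, PSI-SF and WHOQOL-BREF, and for consent and completion after disclosure. It does not extend to the EPDS, the MINI or the demographic data as baselines.

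Bias and unequal refusal are risks built into the order of steps; the protocol does not show that either will occur, or how large it would be. The power loss from about 80% to about 54%, and the rise in false positives from 5% to about 12%, both rest on assumed inputs: 29 per arm, correlation 0.5, and a 0.2 SD shift gone by post-treatment. The power figure also assumes a true effect of 0.75 SD. The power loss is the more plausible of the two, since relief or disappointment points that way.

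The issue belongs to the protocol and not to an analysis plan. Baseline adjustment would reduce the distortion, but no analysis can recover scores unaffected by knowledge of the arm once the scales have been taken in this order.

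**What to change.** Reorder the steps in Section III, items 3, 4 and 5:

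1. After the telephone screen, give every eligible woman one common information and consent form covering both arms.
2. Have her complete the DASS-21, PSI-SF and WHOQOL-BREF online.
3. Randomise and disclose the arm only after that baseline is submitted.
4. Give the arm-specific instructions, and the CEQ for the TAICBT arm, after allocation.
5. State that the pre-allocation EPDS is the depression baseline.

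Any baseline shift caused by knowing the arm is then excluded by design, and women who decline the form or do not finish the survey drop out before randomisation.

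The cost is an ethics amendment and one merged consent form, with the same survey and the same staff. Slightly more screening contacts will be needed per woman randomised, because those who do not finish the baseline survey are never allocated.
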